6.2 Dual-target Magnetic Stimulation Treatment Procedure

During the treatment process: Determine the stimulation plan and begin peripheral stimulation before central stimulation. Adjust the chair to a horizontal angle of 10-20°, instruct the patient to lie prone on the chair, and align the center of the circular coil with the S3 region, stimulating until a contraction of the anal sphincter or a dorsiflexion response is felt, indicating correct positioning. Once the position is confirmed, use single-pulse stimulation to determine the stimulation intensity, and perform repeated peripheral magnetic stimulation according to the plan. Adjust the chair so that the patient sits upright, and measure the RMT during the initial treatment to determine the patient's magnetic stimulation intensity. The rTMS stimulation intensity is set to 120% of the RMT.

Assisted positioning device: Determine the stimulated cortical location based on the positioning cap; for patients with major depressive disorder, stimulate the left DLPFC, and for patients with generalized anxiety disorder, stimulate the right DLPFC, following the central magnetic stimulation protocol.

6.3 Peripheral Magnetic Stimulation Treatment Protocol

Implement rPMS according to the same procedure as the dual-target magnetic stimulation group. All parameters are the same as those in the dual-target magnetic stimulation group.

6.4 Sham Stimulation Group Treatment Procedure

Both peripheral and central magnetic stimulation use a coil that can produce sound but does not generate a magnetic field. The other parameters and procedures are the same as those in the dual-target magnetic stimulation group.

6.5 Treatment Plan

A treatment course will consist of 20 sessions, with five sessions per week, one session each day. The completion of the 20th treatment will mark the end of the course. Follow-up will be scheduled 8 weeks after the end of the course. During the study, patients may receive oral medication, and the specific medication and dosage must be recorded at the time of enrollment. If there are any significant adjustments to the type and dosage of the medication, they need to actively inform the therapist.

7. Follow-up Plan

(1) Assessment, follow-up plan and content: Patients need to return to the hospital for evaluation before treatment, at the end of each weekly treatment, and 8 weeks after the treatment course ends. The assessment includes the patient's pelvic pain score/NIH-CPSI, DASS-21 scale, SF-36 scoring scale, pelvic floor surface electromyography, and pudendal nerve motor evoked potentials.

(2) Establish a complete database and implement a follow-up mechanism managed by dedicated personnel.

(3) Follow-up time points: Before treatment, at the end of each weekly treatment, and up to 8 weeks after the end of the treatment course.

(4) Outside of the time points for in-hospital assessments and follow-up visits, dedicated follow-up medical staff will conduct tracking follow-ups through phone calls, written questionnaires, emails, and other forms.

8. Evaluation Indicators for Research Results

8.1 Main Efficacy Indicator: Pain Score

(1) Pelvic Pain Rating Scale (for women): It includes the patient's basic information, detailed changes in symptoms, and the effectiveness of previous treatments. It uses pain exacerbated and relieved by sexual activity and menstruation as the starting point for medical history inquiries. Additional details include symptoms related to exercise, urinary, and bowel function.

(2) NIH-CPSI (for men): It mainly consists of three parts, assessing pain or discomfort caused by chronic prostatitis, urinary symptoms, and the impact on quality of life, with a total of nine questions. It is characterized by objectivity and convenience, is quickly accepted by patients, and can provide important references for research and clinical work.

8.2 Secondary Efficacy Indicators:

(1) Anxiety and Depression Scores (DASS-21): For depression, the cutoff values for mild, moderate, and severe depression are 10, 14, and 21, respectively; for the anxiety scale, the cutoff values for mild, moderate, and severe anxiety are 8, 10, and 15, respectively; for the stress scale, the cutoff values for mild, moderate, and severe stress are 15, 19, and 26, respectively.

(2) Surface Electromyography of the Pelvic Floor Muscles: Participants will lie in a supine position, with their upper and lower bodies forming an angle of approximately 120°, and their feet naturally rotated outward. An electrode will be placed in the rectum to collect surface electromyography data from the pelvic floor muscles, while abdominal electrodes will monitor abdominal muscle activity. Before the examination, participants will be instructed to urinate and defecate, taught how to properly contract and relax the pelvic floor muscles, and informed about the assessment process. They will learn how to quickly contract and hold the contraction for 10 seconds. Participants will contract and relax their pelvic floor muscles based on verbal prompts to record surface electromyography values.

(3) Pudendal nerve motor evoked potentials: Participants will be instructed to use a glycerin suppository for rectal evacuation and to assume a prone position. A magnetic stimulation coil will be placed 3-5 centimeters lateral to the midline of the S3 plane, stimulating both sides simultaneously at 55-60% of the maximum output intensity. A surface electrode will be placed in the rectum to record the anal sphincter, and a ground electrode will be connected to the wrist. The amplifier's sampling bandwidth is 5-2000 Hz, with a sensitivity of 3 milliseconds per division and an analysis time of 30 milliseconds. Five successful recordings will be made, and the average results will be taken.

(4) SF-36 QoL Scale: A generic quantitative scale consisting of 36 items, covering eight domains including physical functioning, physical role, bodily pain, general health, vitality, social functioning, emotional role, and mental health.

Adverse events occurring after surgery should be recorded using the adverse event report form. If it is a serious adverse event, please fill out the serious adverse event form and report it to the clinical trial leader and the ethics committee within 24 hours. Additionally, please complete the SAE report form.

8.3 Safety Indicators

Blood routine, liver and kidney function tests, and electrocardiogram: Check whether the examination and treatment measures have caused harm to the participants.

9. Safety Evaluation:

9.1 Benefits

According to relevant reports, chronic pelvic pain syndrome has shown a high incidence both domestically and internationally. Patients with this condition who also have mental health disorders have limited treatment options and poor efficacy. Therefore, it is particularly important to find new effective treatment methods for chronic pelvic pain syndrome accompanied by mental health disorders. Currently, with the development of non-invasive neuromodulation technology, transcranial magnetic stimulation has been widely used in the treatment of mental and psychological disorders, and peripheral magnetic stimulation has also shown certain efficacy in pain treatment. Our team, based on clinical experience and literature reports, has adopted dual-target magnetic stimulation to treat patients with chronic pelvic pain syndrome accompanied by mental health disorders, observing its clinical effectiveness and safety. We hope to provide treatment references for more physicians focusing on pelvic pain syndrome and bring health and hope to a large number of patients.

9.2 Risk

(1) If you experience any discomfort during the study, or if there are any new changes in your condition, or any unexpected situations, regardless of...

Whether it is related to the research or not, you should promptly inform your doctor, who will make a judgment and provide appropriate medical treatment.

(2) Transcranial magnetic stimulation has been recommended for the treatment of anxiety and depression by multiple guidelines and consensus both domestically and internationally. A review of our team's previous studies on peripheral magnetic stimulation and transcranial magnetic stimulation shows that only a very small number of patients experienced pain at the stimulation site and transient hearing loss, with no serious adverse reactions. This has confirmed that the trial is safe and effective, with controllable risks.

9.3 Risk Prevention Measures

9.3.1 Guiding Principles:

(1) Prevention is key: Upon discovering cases, report them promptly and actively take effective measures to control the progression of the disease.

(2) Legal Management: Throughout the entire process of clinical trials, relevant laws and regulations must be implemented. Any unexpected events and adverse events should be reported promptly. Legal management should be enforced during the entire control and treatment process, and legal responsibility should be pursued for any violations.

(3) Hierarchical Responsibility: In clinical trials, standardized operating procedures are strictly implemented, and the entire process is monitored and inspected regularly or irregularly to ensure timely detection and prompt treatment.

(4) Rapid Response: Establish early warning and rapid medical response systems, strengthen the reserves of human, material, and financial resources, enhance emergency handling capabilities, and follow the principles of early detection, timely reporting, reliance on science, and decisive measures for prompt and accurate handling.

9.3.2 Organizational Management:

(1) Leadership Organization: Under the leadership of the dean, the Medical Affairs Department is specifically responsible for organizing and implementing the handling of emergencies. It is responsible for supervising the medical services provided by the hospital's medical staff, inspecting the practice of medical personnel, accepting complaints, and providing consultation services. It also cooperates and coordinates with related disputes and their resolution.

(2) Command System: Incorporate the harm to subjects and emergencies in clinical trials into the hospital's rescue operations and normal medical dispute resolution processes.

(3) Daily management work: The office of the clinical trial institution is responsible for daily business management, specifically overseeing business guidance for clinical trials, organizing management and quality control, conducting supervision and inspection, as well as handling daily information communication, organizational coordination, and reporting of emergencies.

(4) Participants: Medical, nursing, technical professionals from various specialized departments, as well as mental health personnel.

9.3.3 Preventive Measures:

(1) Assurance from the Ethics Committee: Before the clinical trial begins, the trial protocol must be reviewed and approved by the Ethics Committee and signed off before implementation; during the clinical trial, any modifications to the trial protocol must be approved by the Ethics Committee before they can be executed; any harm to subjects or serious adverse events that occur during the trial must be reported to the Ethics Committee.

(2) Assurance from the Principal Investigator: The head of the clinical research project should have at least a bachelor's degree and a senior professional title, possess the specialized knowledge and experience required by the clinical trial protocol, be familiar with the materials and literature related to the clinical trial provided by the sponsor, and have the authority to allocate the personnel and equipment necessary for conducting the trial; they should also have the ability to handle adverse events and the responsibility to report such events in a timely manner.

(3) Researcher's Assurance: Familiarity with the standard operating procedures for adverse event reporting; before the clinical trial begins, all rescue equipment and emergency medications are in place in a timely manner to ensure that participants receive immediate treatment in the event of harm or emergencies.

(4) Assurance to the subjects: Subjects must voluntarily participate and have a thorough understanding of the research project; the rights of subjects to protect themselves must always be respected; measures should be taken to respect the privacy of subjects, maintain the confidentiality of their data, and minimize the impact on their physical and mental well-being as well as their personality; after informing the subjects of all aspects of the trial, subjects must voluntarily confirm their consent to participate in the clinical trial process, which must be documented with a signed and dated informed consent form.

(5) Institutional Guarantees: Establish and improve the quality assurance system; ensure the qualifications of principal investigators; guarantee the facilities of various specialized departments; ensure the quality of clinical trial protocols; control the quality of clinical trial data; establish work systems, design specifications, and standard operating procedures that comply with GCP management regulations. Develop emergency plans for subject harm and unexpected events: establish a handling team for subject harm and unexpected events to ensure that subjects or patients receive timely treatment in the event of harm or unexpected incidents during the medical process; prepare and coordinate the prevention of subject harm and unexpected events, on-site control, emergency response, and other resources and technical support.

9.3.4 Adverse Events:

Adverse events (AEs) refer to any factors and incidents that may affect a patient's treatment outcomes, increase the patient's suffering and burden, potentially lead to medical disputes or accidents, and impact the normal operation of medical work and the personal safety of medical staff during clinical diagnosis and treatment activities as well as hospital operations. These events do not necessarily have a causal relationship with the treatment. Therefore, adverse events can be any negative and unexpected signs (including abnormal laboratory findings) and symptoms, or diseases that are temporally related to the use of medical products, regardless of whether they are considered related to the study.

During the research process, disease progression or deterioration (including increased pain and exacerbation of mental health issues due to disease progression) should be considered part of the efficacy evaluation and should not be reported as adverse events or serious adverse events.

During the clinical research period, all adverse events that occur will be reported on the adverse event page of the Case Report Form (CRF). The severity of adverse events will be classified using the "Classification and Grading Standards for Adverse Events in Medical Quality Safety" established according to China's "Medical Quality Management Measures" (https://www.gov.cn/zhengce) and will be reported in detail as required on the CRF.

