9.3.4.1 Definition of Serious Adverse Events

Serious Adverse Events (SAE) refer to any adverse medical condition that occurs during the treatment process and meets one of the following criteria:

(1) Lethality (causing death; note: death is the consequence, not the event);

(2) Life-threatening (Note: "Life-threatening" refers to the immediate danger of death to the patient at the time the event occurs, and does not refer to a hypothetical situation where a more severe event could lead to death.)

(3) Leads to hospitalization of the patient or an extended hospital stay;

(4) Resulting in lifelong or severe disabilities/functional impairments;

(5) It is of significant importance in medicine or requires intervention measures to prevent the occurrence of any of the aforementioned consequences.

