9.3.4.2 Causal Relationship

The following standards should be used to assess the relationship between adverse events and treatment:

(1) Very likely related: This category refers to adverse events that are considered to be related to clinical research with a high degree of certainty. An adverse event can be deemed "very likely related" if it meets the following criteria:

The occurrence of adverse events is reasonably time-related to the intervention measures.

The known patient disease status, environmental or toxic factors, or other treatments used by the patient cannot reasonably explain the adverse events.

(2) Possibly related (must meet the first two criteria): This category refers to adverse events that are unlikely to be related to this study, but cannot be definitively ruled out as having a connection. An adverse event can be considered "possibly related" if it meets the following criteria:

The occurrence of adverse events is reasonably time-related to the intervention measures.

Adverse reactions may be caused by the patient's disease state, environmental or toxic factors, or other concomitant treatments used by the patient.

(3) Possibly unrelated (must have the first two items): This category applies to adverse events that meet the following criteria:

The occurrence of adverse events is not reasonably correlated in time with the intervention measures.

Adverse events are clearly caused by the patient's disease state, environmental or toxic factors, or other concomitant treatments used by the patient.

(4) Irrelevant: This category refers to adverse events that are clearly and unequivocally determined to be caused solely by external factors (such as diseases, environment, etc.) and do not meet the relevance judgment criteria under "possibly irrelevant," "possibly relevant," or "very likely relevant."

It must comply with the ICH guidelines for the management of clinical trial safety data and the definitions and standards for expedited reporting.

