9.3.4.3 Expected Adverse Events

(1) Epileptic seizure;

(2) fainting;

(4) Localized pain, headache, discomfort;

(5) Temporary changes in hearing;

(6) Brief cognitive/neuropsychological changes;

(7) Acute mental changes;

(8) Others.

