9.3.4.4 Adverse Event Handling Measures

(1) Take necessary treatment measures based on specific circumstances and decide whether to terminate the clinical trial. Detailed records of the symptoms, signs, or laboratory test results, including the time of occurrence, duration, severity, management measures, and progress, should be documented in the medical record. The researcher should evaluate the relevance to the clinical trial, sign, and date the record.

(2) When adverse events are discovered, researchers should immediately address the situation and report it to the project leader, the ethics committee, and the clinical research center. They should determine the necessary diagnostic and treatment measures based on the patient's condition and decide whether to terminate the clinical trial. All adverse events should be investigated and tracked, with detailed records of the handling process and outcomes maintained until the issue is properly resolved or the patient's condition stabilizes. If there are abnormal test results, they should be monitored until they return to normal. The method of follow-up can be chosen based on the severity of the adverse reaction, including hospitalization, outpatient visits, home visits, phone calls, or correspondence.

(3) Reporting of Adverse Events: During the study period, regardless of the treatment received by the patient, any serious adverse events or serious laboratory test result abnormalities that occur must be documented by the investigator on an adverse event report form and reported to the project leader, ethics committee, and clinical research center within 24 hours of becoming aware of them.

SAE report contact person: [name](Chengdu Anorectal Hospital Pelvic Floor Center)

Contact person: [name](Academic Committee of Chengdu Anorectal Hospital)

Mobile phone：[name]

Email：[contact]

Address: [name].

(4) Recording: Researchers should document the subjects' symptoms, signs, laboratory tests, the time of onset of damage, duration, severity, treatment measures, and progress in the original medical records and CRF forms, ensuring that the records are true, accurate, complete, timely, and legal. They should fill out the serious adverse event report form, sign it, and indicate the date; the original records should include the time, reporting method, and the reporting institution.

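### Section 9.3.4 bars worsening attributed to disease from AE and SAE reporting even when it is serious, contradicting the protocol's other safety rules, so serious psychiatric or pain events could go unreported

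*Protocol*

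**What the plan says.** Protocol section 9.3.4 first defines adverse events broadly: they count "regardless of whether they are considered related to the study". The next paragraph takes out disease progression or deterioration, "including increased pain and exacerbation of mental health issues due to disease progression", and says that these "should be considered part of the efficacy evaluation and should not be reported as adverse events or serious adverse events". It names serious adverse events expressly and gives no exception for hospitalisation, threat to life or death. It does not say who decides that a worsening is due to disease progression, or by what criteria.

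The neighbouring sections read differently:
- 9.3.3 (ethics committee assurance): harm to participants and serious adverse events must be reported to the committee.
- 9.3.4.1: an event is serious if, among other criteria, it "Leads to hospitalization of the patient or an extended hospital stay".
- 9.3.4.2: an adverse event is graded for causality, and the lowest grade is for events "clearly and unequivocally determined to be caused solely by external factors (such as diseases, environment, etc".
- 9.3.4.3: the expected adverse events include "Acute mental changes".
- 9.3.4.4: "any serious adverse events or serious laboratory test result abnormalities that occur must be documented by the investigator", and reported within 24 hours to the project leader, the ethics committee and the clinical research center.

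**The concern.** Pain and mental state are both the conditions under study and places where stimulation could do harm. Under inclusion criterion 3, every participant has generalized anxiety disorder or major depressive disorder, and the dual-target arm has the prefrontal cortex stimulated (section 6.1). Whether a worsening comes from the disease or from the treatment is what a three-group safety comparison should help to show. The exemption makes the answer for the individual patient a condition of reporting.

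Two things are at stake. The ethics committee might not hear of a serious event that the rest of the protocol would send to it. The between-arm account of serious psychiatric and pain events might also be incomplete, although safety is part of the stated objective (section 2).

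**Working it through.** No figure in the plan is at issue, so the check is textual. Take a hypothetical case: a participant in the dual-target group is admitted to hospital during treatment with an acute worsening of depression.

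1. **AE definition (9.3.4).** The admission follows a negative sign or symptom in time relation to treatment, and cause does not matter. It is an adverse event.
2. **Seriousness (9.3.4.1).** Hospitalisation is a criterion. The event is serious.
3. **Causality (9.3.4.2).** Three of the four grades allow for or assert the patient's disease as the explanation: the event may be caused by the disease state (possibly related), is clearly caused by it (possibly unrelated), or is caused solely by external factors, with diseases as an example (irrelevant). Disease causation is thus a grade given to a recorded event, not a reason to leave it unrecorded.
4. **Expected events (9.3.4.3).** An acute mental change is on the list.
5. **Duty to report (9.3.3, 9.3.4.4).** It goes to the ethics committee, within 24 hours as a serious event.
6. **Exemption (9.3.4).** If someone attributes the worsening to disease progression, it is not to be reported as an AE or an SAE. The event then leaves the category to which the grading in step 3 and the 24-hour duty in step 5 apply.

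Steps 1 to 5 and step 6 give opposite instructions for the same admission. Only the attribution decides between them.

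**Would the efficacy evaluation record it instead?**
- DASS-21, the graded items of the female pelvic pain sheet, and NIH-CPSI ask about the past week. SF-36 mostly asks about the past 4 weeks (Appendices 3 to 6).
- Between the end of treatment (t4) and the next scheduled assessment (t5) there are 8 weeks (Appendix 2). The one-week scales leave 8 − 1 = 7 of those weeks uncovered, and a 4-week recall leaves 8 − 4 = 4.
- None of these scales asks about admission. DASS-21 has no suicidality item; item 7, on life being meaningless, is the nearest.
- The safety indicators in 8.3 are blood tests and ECG.
- Exit criterion 2 in section 3.3 withdraws a patient whose changed condition prevents continuing, so later scale scores may be lost as well.

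**Scale only.** With 22 patients per arm (section 5.1), one event is 1/22 = 4.5% of an arm and two are 2/22 = 9.1%. The exact 95% interval for 1 of 22 is 0.1% to 22.8%. This shows how much a single event weighs in an arm of this size. It does not estimate how many would be lost.

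**The case against.** The strongest defence has four parts.

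- **The bar is conditional and other duties favour reporting.** It covers only worsening due to disease progression. Section 9.3.3 speaks of harm to participants, which is wider than the SAE label, and 9.3.4.2 requires compliance with ICH safety-reporting standards. A reader might infer that a psychiatric admission or suicidal crisis would go unreported. The text does not support that: it supports that one can. The defence does not remove the conflict, because an investigator who reports must set aside an explicit and more specific instruction.
- **Worsening is moved to efficacy, not discarded.** The pain scales and DASS-21 are collected in all arms from t0 to t5 by a separate evaluator (section 14.4), so average worsening is compared without any attribution. Seizure, fainting, headache, hearing change, laboratory and ECG findings are unaffected. This stands, and it rules out the inference that the safety comparison as a whole is undermined. The gap is discrete serious events. Section 7 also provides for telephone and other contact between visits, which might bring an admission to light, but it names no field for one and does not lift the exemption.
- **The pain overlap is weaker.** Localised pain in 9.3.4.3 can be pain at the stimulation site, a different event from progression of pelvic pain. The direct clash with that list concerns acute mental changes.
- **Severe mental illness is excluded (criterion 12).** This limits the risk only in part, since the randomisation form in Appendix 7 lets severe depression or anxiety be ticked for an enrolled patient.

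The safety statement in section 9.2 describes the team's earlier studies. It should not be read as a conclusion planned for this trial.

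**Conclusion.** The contradiction is plain on the text: 9.3.4 exempts disease-attributed worsening without regard to seriousness, while its own AE definition, 9.3.3 and 9.3.4.1 to 9.3.4.4 would have a serious case recorded, graded and reported. Followed literally, the exemption can drop serious psychiatric or pain events from the safety data. It should be corrected.

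The consequence is conditional. It rests on such an event occurring, on its being attributed to disease progression, and on the specific exemption being followed over the general duties. The documents give no rate for psychiatric admission or suicidal crisis, so no expected number of lost events can be stated.

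A reader might also infer that losses would differ by arm. The person giving treatment acts on the allocation (section 14.4), so this is possible if that person takes part in the attribution. No section says who attributes or when, so it remains a possibility.

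**What to change.** Reconcile 9.3.3 and 9.3.4 to 9.3.4.4 with a paragraph in 9.3.4:
- Limit the exemption to changes in scheduled scale scores and to non-serious, expected fluctuation of pain or mood. Say how a non-serious acute mental change, which 9.3.4.3 lists as an expected adverse event, is to be treated.
- State that any worsening of pain or mental state that meets a criterion in 9.3.4.1 is reported as an SAE under 9.3.4.4 whatever its presumed cause, with causality graded separately under 9.3.4.2.
- Tabulate these events by arm.

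Recording every non-serious worsening as an adverse event is not needed to resolve the contradiction and would largely repeat the weekly scales.

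The cost is one paragraph and a few more report forms. Treatment, visits and staffing do not change.
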